**Methods:**

This protocol describes the design of a single-blind, two-arm, parallel-group, intensive longitudinal randomized controlled trial. Participants of this study are adult smokers who smoke at least one cigarette per day and intend to quit smoking at a self-set quit date. Blocking as means of group-balanced randomization is used to allocate participants to intervention or control conditions. Both intervention and control group use a smartphone-compatible device for measuring their daily smoking behavior objectively via exhaled carbon monoxide. In addition, the intervention group is instructed to use the SmokeFree Buddy app, a multicomponent app that also facilitates smoking-cessation specific social support from a buddy over a smartphone application. All participants fill out a baseline diary for three consecutive days and are invited to the lab for a background assessment. They subsequently participate in an end-of-day diary phase from 7 days before and until 20 days after a self-set quit date. Six months after the self-set quit date a follow-up diary for three consecutive days takes place. The primary outcome measures are daily self-reported and objectively-assessed smoking abstinence and secondary outcome measures are daily self-reported number of cigarettes smoked.

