### The SmokeFree buddy app

As part of the tobacco prevention campaign in Switzerland the Federal Office of Public Health (FOPH) and its partners developed a smartphone app –the SmokeFree Buddy app - to encourage smokers’ intention to quit and to offer social support interactively from a self-chosen person (buddy) while quitting smoking. The SmokeFree Buddy app was developed from experts based on the empirical and theoretical evidence of social support from a social network member for smoking cessation. Mobile interventions have the potential to intervene at any time, in a tailored manner and during actual experiences in people’s everyday life [40]. The SmokeFree Buddy app, thus, aims at enabling smokers to quit with the help of a self-chosen buddy from one’s social network and offers the possibility of enhancing social support resources and availability directly after a self-set quit attempt in smoker’s everyday life. The buddy then gets instructed via the smartphone app on how to support the smoker during his/her quit attempt. In addition to self-reported smoking behavior the present RCT uses an objective device to assess smoking abstinence via a “smokerlyzer” with a corresponding smartphone app and is therefore, the first study assessing smoking abstinence objectively on a daily basis.

A general criticism on standard RCT’s is that the level of longitudinal assessment is usually on a macro-time level (e.g., baseline and a 1 month follow-up). This is also the case for intervention studies on social support in the context of smoking cessation (i.e., [11, 37, 38]). However, relatively little is known on when an intervention reaches its effect and what time window would be appropriate to capture it. As such, the choice for the follow-up time points is often made on an arbitrary basis. By using micro-time assessments (e.g., daily) during an ongoing intervention, it is possible to answer questions on how an intervention effect unfolds over time, when it reaches its maximal effect and whether it is maintained or levels off quickly [42]. Moreover, it allows investigating how people respond differently to the intervention. In the present study, we combine micro-time and macro-time assessments by using an intensive longitudinal intervention design with three end-of-day diary periods across 6 months. The 6 months time period was chosen for better comparability with previous studies using a six-month follow-up.

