## Methods/design

This single-blind, two-arm, parallel-group, randomized controlled trial comprises an intensive longitudinal design with three end-of-day diary periods: A *baseline diary* (3 consecutive days), a *challenge diary* from 7 days before the self-set quit date, on the self-set quit date until 20 days after the self-set quit date (28 consecutive days) and a *follow-up diary* 6 months after the self-set quit date (3 consecutive days). See Fig. 1 for the longitudinal design.

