### Statistical analysis

Upon completion of data collection, data will be cleaned and prepared for data analyses. Primary and secondary outcome variables and mediating mechanisms will be checked for distribution, outliers and missing patterns, and appropriate steps will be taken where necessary (cf., [57]). All analyses follow intention-to-treat principles, taking advantage of all available data points. Low levels of missings will be expected, with previous studies showing high completion rates (> 90%, e.g., [26]). Intermittent missing data will be handled by maximum likelihood (MI) estimation. Participants who completely drop out of the study will be treated as smokers. Preliminary analysis will include a randomization check to test for baseline differences between intervention and control participants. For the main data analysis, we will use multilevel modeling to account for the nested structure of daily measures within individuals [58]. To examine the first research question on the effects of the intervention using the daily diary, a set of generalized linear mixed models will be performed in SPSS and R. Daily smoking abstinence will be modeled as a function of time group and group by time, testing group differences at the quit date (model 1) and 3 weeks later (model 2) by centering the time variable accordingly. Model 3 will separately test group differences 6 months later. For the primary outcomes of subjectively and objectively reported smoking abstinence (dichotomous), we will use mixed logistic regression analyses. For the secondary outcome of subjectively reported number of cigarettes smoked, a count variable, we will use a negative binomial model with zero inflation [59, 60]. To test the third research question on the mediating mechanisms of the intervention effect, we will use a multilevel approach to mediation analysis based on multilevel structural equation models [61, 62].

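### Models 1 and 2 as written put one time slope per group on a diary that crosses the quit date; unless they are limited to days 0 to 20 or given a quit-date phase, the quit-date contrast can be attenuated and the 3-week contrast distorted

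*Protocol article*

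**What the plan says.** The Statistical analysis section gives the model for the primary outcomes: "Daily smoking abstinence will be modeled as a function of time group and group by time". For the two dichotomous abstinence outcomes, "we will use mixed logistic regression analyses". The first two time points are handled by "testing group differences at the quit date (model 1) and 3 weeks later (model 2) by centering the time variable accordingly". The third is kept apart: "Model 3 will separately test group differences 6 months later".

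The diary that supplies models 1 and 2 is described in Methods/design as running "from 7 days before the self-set quit date, on the self-set quit date until 20 days after the self-set quit date". That is 7 days before the quit date and 21 days from it on, 28 in all. On data use, the Statistical analysis section says: "All analyses follow intention-to-treat principles, taking advantage of all available data points".

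The article names no pre/post-quit phase term, knot or curvature, and does not limit models 1 and 2 to days from the quit date on. It also does not call time linear, and does not say outright that the 7 pre-quit days enter.

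**The concern.** Re-centring changes the group coefficient only if time is a numeric variable. Models 1 and 2 are therefore one fit read at two days. With one time term and one interaction, each group has one straight line on the log-odds scale.

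The article's own premises point to a different shape. Participants smoke daily at entry, so abstinence before the quit date should be near zero. They try to stop on day 0. The Background says that most relapses fall in the first weeks. The expected course is near zero, then a step up, then a decline, and a line through all 28 days cannot follow it. Pre-quit days, on which the groups should look alike, then pull on the fitted group difference at day 0. The slope mostly reflects the step.

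Two of the three time points for the primary outcomes are read from this model. The daily design is also justified by the claim that "it is possible to answer questions on how an intervention effect unfolds over time, when it reaches its maximal effect". An effect that is present early and gone by 3 weeks is one that the trial wants to recognise, and it is a case that this line handles poorly.

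**Working it through.** **The plan's own figure.** The only figure that can be reproduced is the sample size: 27% against 51%, power 0.80, two-sided 0.05.

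n per arm = [1.96·√(2·0.39·0.61) + 0.842·√(0.27·0.73 + 0.51·0.49)]² / 0.24² = (1.352 + 0.563)² / 0.0576 ≈ 63.7, so 64 per arm and 128 in total. This agrees with the Power analysis section. It does not depend on the time model, so it neither supports nor undermines the point.

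**Inputs from the article.** Days -7 to +20; 80 per arm; terms time, group and group × time; mixed logistic model; 27% control abstinence and a 24-point difference (the 27% is stated for 6 months).

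**Inputs assumed.** Pre-quit abstinence 3% in both groups (10% as sensitivity); the daily rates at days 0 and 20 shown below; random-intercept SD 2; no random slope.

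**Data-generating model.** logit P(abstinent) = a + u, with u ~ N(0, 2²). The value of a is constant before day 0, steps at day 0, and follows a straight line to day 20. Each a is chosen so that the population-average rate matches the stated percentage. For control at 50% falling to 27%, a goes from 0 to -1.62, a slope of -0.81 per 10 days. The true group log-OR at 50% against 74% is 1.70.

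**Fits.** Random-intercept logistic regression by maximum likelihood, with the same terms, (a) on all 28 days and (b) on days 0 to 20 only. The constant, fading and no-effect rows rest on 120, 120 and 200 simulated trials with 81-point quadrature. The other rows rest on 150 trials with 25-point quadrature.

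| Scenario (control/intervention, day 0 → day 20) | Day 0: true | all 28 days | days 0–20 | Day 20: true | all 28 days | days 0–20 |
|---|---|---|---|---|---|---|
| Constant effect, relapse: 50/74 → 27/51 | 1.70 | 0.83 | 1.70 | 1.68 | 1.76 | 1.70 |
| Same, pre-quit abstinence 10% | 1.70 | 0.77 | 1.65 | 1.68 | 1.78 | 1.64 |
| Constant effect, no relapse: 27/51 → 27/51 | 1.68 | 1.04 | 1.67 | 1.68 | 1.84 | 1.67 |
| Fading: 27/51 → 27/27 | 1.68 | 0.94 | 1.69 | 0 | 0.46 | 0.01 |
| Growing: 50/50 → 27/51 | 0 | 0.15 | 0.04 | 1.68 | 1.38 | 1.70 |
| No effect: 50/50 → 27/27 | 0 | -0.01 | -0.03 | 0 | -0.01 | -0.01 |

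**Quit date.** Where an effect exists from day 0, the 28-day fit returns 0.77/1.70 = 45% to 1.04/1.68 = 62% of the true log-OR. In the first row that is an odds ratio of e^0.83 ≈ 2.3 against e^1.70 ≈ 5.5.

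**Three weeks.** The error is 0.08 for a constant effect with relapse and 0.16 without relapse (1.84 against 1.68). It is larger when the effect changes over time: +0.46 when it fades, with a false positive in 31% of runs, and -0.30 when it grows.

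**Slopes per 10 days (first row).** Control +0.62 against a true -0.81; intervention +1.09 against -0.82. A group × time coefficient of 0.47 appears where the truth is -0.01, and is significant in 98% of runs. With no effect, both slopes are still +0.63 against -0.81.

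**A second set of assumptions.** 4,000 smokers, 2% pre-quit abstinence conditional on the random intercept, SD 2. True (day 0, day 20) log-ORs of (1.05, 1.05) came back as (0.55, 1.26), and (1.05, 0.00) as (0.44, 0.27). The quit-date attenuation is the same, 0.55/1.05 = 52%. The day-20 error under a constant effect is larger here, at 0.21.

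**The case against.** The strongest reply is that the straight line through all 28 days is an inference. The article does not use the word linear and does not say that pre-quit days enter. The two anchors, the quit date and 3 weeks later, are the start and end of the post-quit window, so a time axis that begins at day 0 fits the text equally well. In that case the problem disappears. The statement on using all available data belongs with intention to treat and missing data. It cannot define the analysis window: read literally it would also bring in the baseline and 6-month diaries, and the latter has its own model. All of this stands, and it is why the point is conditional.

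It may also be said that a condensed article leaves time coding to the full plan. That is only partly an answer. The article does fix the terms and the centring for the main analysis, and those terms, applied to the diary it describes, do not suit the expected course.

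A reader might go further and infer that the group effects at both time points are biased whatever the truth. The calculations do not support that. With no effect the misfit is the same in both groups and the contrasts centre on zero. (The day-20 test rejected in 9.5% of 200 no-effect runs, too few to rest a claim on.) A reader might also infer that the trajectory aim fails. The article introduces these models for its first research question, not for aim 2, so the wrong-signed slope is a warning against using them to describe trajectories and not a defect in a stated aim 2 analysis.

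Finally, the intervention group uses the app from day -7, so equal pre-quit rates are an assumption, as are the daily rates and the random-intercept SD.

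**Conclusion.** The point holds in conditional form. As written, models 1 and 2 have one slope per group, no quit-date phase and no stated restriction to post-quit days. If all 28 days enter and a group effect exists from the quit date, the quit-date contrast is attenuated to about half (45% to 62% of the true log-OR across the scenarios run). The 3-week contrast is distorted when the effect fades or grows, and nearly right in the main constant-effect scenario. The fitted time slope can have the wrong sign.

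Model 3 at 6 months is unaffected, and so is the sample size. The direction follows from the step at the quit date. The sizes rest on assumed daily rates, 3% or 10% pre-quit abstinence and a random-intercept SD of 2, none of which the article gives. The documents do not establish that the investigators intend the 28-day fit. They leave it open, and it should be closed before the data are analysed.

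**What to change.** State in the Statistical analysis section which diary days enter models 1 and 2. Either of two changes is enough:

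- Fit models 1 and 2 on days 0 to 20 only, with the terms already planned. In the scenarios run, this brought the contrasts to within about 0.05 of the true log-OR.
- Keep all 28 days and add a pre/post-quit phase term with its group interaction.

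Take the day-0 and day-20 group contrasts from that one model, and name day 20, the last challenge-diary day, as the 3-week point. A flexible post-quit time course for describing trajectories under aim 2 is optional and not needed for the two contrasts.

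The cost is analysis wording, plus a few more parameters if the phase model is chosen. The first option is simpler because abstinent pre-quit days will be few: at the assumed 3%, about 0.03 × 7 × 80 ≈ 17 per group, which makes the phase-by-group term poorly estimated. Data collection and sample size do not change.

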### Power analysis

To secure adequate power for the main analysis of the intervention effect on smoking abstinence at the quit date, 3 weeks and 6 months later, we performed a priori sample size calculations using the G*Power program [63]. Based on a power of 0.80 and a two-tailed Type 1 error probability of .05, a total sample size of *N* = 128 is suitable to detect a 24% difference in smoking abstinence for the intervention group, drawing on meta-analyses of mobile-phone interventions on short and long-term smoking abstinence (RR’s between 1.7 and 2.1 [16, 17];). We assumed an abstinence rate of 27% in the control group 6 months after the self-set quit date, based on own previous studies using a highly comparable, albeit correlational, design with daily diaries around a self-set quit date in smokers and their romantic partners [64, 65]. Moreover, attrition rates between 20% (e.g., [31]) 6 months after the self-set quit date, or below 30% [15] have been reported. Thus, assuming an attrition rate of 25%, the targeted sample size is *N* = 160 smokers (*n* = 80 per group) and an additional *N* = 80 buddies.

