### Randomization

The randomization comprises a random assignment to one of the two groups (intervention group and control group). Blocking as means of restricted randomization is used: To meet balance and predictability criteria [44, 45] variable blocks (4, 6, 8) are used. Within a block of participants, 50% are assigned to the intervention group and the control group. Before the beginning of the study, a computerized random-number generator (http://www.randomization.com) is used for sequence generation of blocks. This allocation sequence is generated by an assistant not part of the study team and to ensure allocation concealment concealed in a set of sealed, numbered envelopes until group assignment. On the day of the background assessment in the lab, the interviewer conducting the session opens the appropriate numbered envelope and prepares the study material accordingly. Throughout the study, participants are blinded to the group assignment (i.e., single-blind RCT).

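### The target of 160 smokers allows for 20% attrition, not the stated 25%, so the sample-size figures for the 6-month comparison do not agree

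*Protocol article*

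**What the plan says.** The Power analysis section of the protocol article sets out the calculation in this order:

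- Design values: "Based on a power of 0.80" and "a two-tailed Type 1 error probability of .05".
- A total of 128 smokers "is suitable to detect a 24% difference in smoking abstinence for the intervention group".
- The control rate: "We assumed an abstinence rate of 27% in the control group 6 months after the self-set quit date". With the 24-point difference, this implies 51% in the intervention group.
- Attrition seen elsewhere: 20% in one study, and "6 months after the self-set quit date, or below 30% [15] have been reported".
- The conclusion: "Thus, assuming an attrition rate of 25%, the targeted sample size is" 160, that is 80 per group, plus 80 buddies.

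Two other places bear on the point. The Randomization section says that within a block "50% are assigned to the intervention group and the control group", which is 1:1 allocation. The Statistical analysis section commits to intention-to-treat and classifies participants who leave the study completely as smokers.

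**The concern.** The target is derived from the 25% attrition figure, so 160 recruited should leave the required 128 after a 25% loss. It leaves 120. The percentage was added to the number needed at the end, when it should have been taken off the number recruited at the start.

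The sample-size statement is what readers will use to judge a null result at 6 months. If its figures are inconsistent, nobody can tell what power the trial was designed to have for that comparison. The Statistical analysis section adds a further difficulty. It keeps dropouts in the analysis as smokers, whereas the attrition allowance treats them as lost. The two sections therefore describe different 6-month analyses.

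**Working it through.** **Inputs.** From Power analysis: two-sided α = 0.05 (z = 1.960), power 0.80 (z = 0.842), p₁ = 0.27, p₂ = 0.27 + 0.24 = 0.51, attrition d = 0.25, target 160. From Randomization: 1:1 allocation. From Statistical analysis: complete dropouts counted as smokers.

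**Step 1. Reproduce 128.** Pooled two-proportion formula, with p̄ = 0.39:

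n = [1.960·√(2·0.39·0.61) + 0.842·√(0.27·0.73 + 0.51·0.49)]² / 0.24² = [1.352 + 0.563]² / 0.0576 = 63.6

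This rounds up to 64 per group, N = 128, as stated. The arcsine formula also gives 128. The continuity-corrected (144), unpooled (122) and one-sided (102) versions do not. The implied risk ratio, 0.51/0.27 = 1.89, lies inside the cited range of 1.7 to 2.1.

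**Step 2. Attrition.**

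- 128 × 1.25 = 160: the stated target.
- 160 × 0.75 = 120: eight short of 128.
- 128 / 0.75 = 170.7: 171, or 172 (86 per group) for equal groups, which is 11 to 12 more than 160.
- 1 − 128/160 = 0.20: the attrition that 160 actually covers.

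**Step 3. Power at 6 months with 160 recruited.** With n per group and p̄ the mean of the two rates:

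power = Φ{[(p₂ − p₁)·√n − 1.960·√(2p̄(1 − p̄))] / √(p₁(1 − p₁) + p₂(1 − p₂))}

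*Reading A: dropouts are lost to analysis.* n = 60: (0.24·√60 − 1.352)/0.669 = 0.758, power 77.6%. At n = 64 the same formula gives 80.2%.

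*Reading B: dropouts count as smokers, and 27% and 51% are completer rates.* With 25% dropout in each arm, the rates become 0.75 × 27% = 20.25% and 0.75 × 51% = 38.25%, and the difference falls to 18 points. n = 80: (0.18·√80 − 1.261)/0.631 = 0.553, power 71.0%. Restoring 80% takes 100 per group, N = 200. With 172 (n = 86), power is 74.1%.

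*Reading C: dropouts count as smokers, and the rates already include them.* All 160 are analysed at 27% against 51%. n = 80: (0.24·√80 − 1.352)/0.669 = 1.189, power 88.3%. The 128 would already give 80%, and no inflation is needed.

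**Step 4. Across the attrition range that the article cites** (160 recruited; 30% is the upper limit of that range):

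| Attrition | Completers | A | B | C |
|---|---|---|---|---|
| 20% | 128 | 80.2% | 75.0% | 88.3% |
| 25% | 120 | 77.6% | 71.0% | 88.3% |
| 30% | 112 | 74.7% | 66.7% | 88.3% |

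On none of the three readings does a 25% loss turn a requirement of 128 into a target of 160 at 80% power.

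**The case against.** A reader might infer from the faulty division that the trial will end with 120 evaluable smokers and miss its 80% power, and that recruiting 172 would put this right. The article does not support that inference. Under its intention-to-treat and dropouts-as-smokers rule, a smoker who leaves still has an outcome and stays in the denominator, so 160 are analysed. Power may then be well above 80% (reading C) or further below it than the division alone suggests (reading B). The control rate is taken from the authors' earlier diary studies, and the article does not say how those studies counted dropouts. Recruiting 172 restores 80% only under reading A; it falls short under B and is unnecessary under C.

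Three further points can be made for the plan:

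- 160 is exactly right at 20% attrition, which the article itself cites.
- Under reading A the shortfall is only about 2.4 points below 80%, small beside the uncertainty in the assumed rates and risk ratios.
- The control rate, and at least the 20% attrition figure, are tied to 6 months, and diary completion above 90% is expected. The calculation therefore shows nothing against the quit-date and 3-week comparisons.

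All of this stands, and it limits the consequence. It does not rescue the sentence: 128, 25% and 160 are all printed in the article and are inconsistent with one another whatever the dropout rule.

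**Conclusion.** The arithmetic error is established from the article alone: a 25% allowance on 128 gives 171 (172 for equal groups), and 160 allows for 20%. The statement needs correction as a description of the 6-month comparison.

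The size of the effect on power is conditional. It is 77.6% in a completer analysis, 71.0% under the article's own dropout rule if the assumed rates are completer rates, and 88.3% if they already count dropouts as smokers. These figures rest on a pooled two-proportion comparison, chosen because it reproduces 128 and not because it is the planned mixed logistic model, and on equal 25% dropout in both arms. That the trial is underpowered is not shown. What is shown is that its stated power does not follow from its stated inputs, and that the power calculation and the analysis section treat dropouts differently.

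**What to change.** Keep the target of 160 and correct the sentence in Power analysis in one of two ways:

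1. State that 160 corresponds to 20% attrition from a requirement of 128.
2. Keep 25% attrition and restate the 6-month power, computed with dropouts counted as smokers as the Statistical analysis section requires.

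With either choice, add a clause saying whether the 27% and 51% rates already count dropouts as smokers. Without it, option 1 repairs the division but leaves the two sections out of step: at 20% attrition, power under the dropouts-as-smokers rule is still 75.0% if these are completer rates. If a larger target is considered instead, 172 should be offered only for a completer analysis; under the dropout rule with completer rates, the figure is about 200.

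The cost is one corrected statement and possibly a less favourable stated power. No additional smokers are needed if the figure is restated, and design, allocation and outcomes do not change.
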